## Randomization process

The participants are randomly assigned to each group after the baseline assessment, when the demographic data are collected. We use concealed randomization assignment and an adequate computer-generated assignment sequence to avoid selection bias. Thus, neither investigators nor the participants’ parents can influence which group the patients are assigned to.

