## Outcome measures

The baseline and follow-up evaluations will be performed by experienced pediatric assessors blinded to the group assignments when the patient is at 1, 4, 6, 12 and 24 months CA.

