### Primary outcome measure

Motor development will be measured using the Peabody Developmental Motor Scales-II (PDMS-II) via the motor quotient. Motor development is measured at 1, 4, 6, 12 and 24 months CA with the PDMS-II by an assessor blinded to the group assignments. The use of the PDMS-II is recommended [40] and has been widely used as a motor development outcome measure for patients with CHD [41–46]. Both fine and gross motor function can be assessed by the PDMS-II. The PDMS-II is valid for children aged from term to 76 months. The PDMS-2 contains six subtests, including reflexes, stationary, locomotion, object manipulation, grasping and visual-motor integration. The results of the subtests may be used to generate a Gross Motor Quotient, a Fine Motor Quotient and a Total Motor Quotient, which are three global indices of motor development. A previous study demonstrated that the PDMS-II had high test-retest reliability and acceptable responsiveness to intervention effects [47].

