
### Sample size calculation

We used GPower3.1.9.2 to perform the power calculation. Our primary outcome measure is the motor quotient measured on the PDMS-II. A difference of the motor quotient score among the three groups of 0.5 SD is considered to be clinically significant. Thus, we must recruit 42 infants in each group to have an 80% chance of detecting this difference among the three groups with a significance level of 0.05 (alpha) on two-sided tests. Considering potential attrition, 49 infants in each group will be recruited.

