## Statistical analysis

The SPSS 20.0 and Microsoft Excel 2013 software will be used for statistical analyses. Demographic data will be described with descriptive statistics, including the mean ± standard deviation (SD). We will use analysis of covariance to compare the primary and secondary outcomes of the three groups. A general linear model will be used to compute mean outcome values adjusted for diagnosis, gender and socioeconomic status (SES), with the group as the fixed factor and diagnosis, gender and SES as covariates. If patients are lost to follow-up, an intention-to-treat analysis will be performed. Statistical significance is set at a p-value less than 0.05.

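### The stated adjustment set leaves out the infant's own pre-randomization 1-month value of the outcome, so precision already paid for is not used

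*Protocol article*

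**What the plan says.** The Statistical analysis section of the protocol article opens the comparison with "We will use analysis of covariance to compare the primary and secondary outcomes of the three groups". The next sentence describes a general linear model giving adjusted means, "with the group as the fixed factor and diagnosis, gender and SES as covariates". No baseline value of any outcome appears in that list, and no section describes a change-from-baseline analysis.

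The baseline value is nevertheless collected, and before allocation. The Randomization process section states: "The participants are randomly assigned to each group after the baseline assessment". The Outcome measures section says "The baseline and follow-up evaluations will be performed by experienced pediatric assessors blinded to the group assignments", with the first visit at 1 month CA. For the primary outcome, the Primary outcome measure section says "Motor development is measured at 1, 4, 6, 12 and 24 months CA with the PDMS-II", listing the 1-month score alongside the four later ones. The Methods/Design section places the start of the exercises at 1 month CA and the main motor aim at 24 months CA.

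**The concern.** A 1-month score taken before allocation cannot be affected by treatment. For a continuous outcome, the infant's own earlier value is often among the better predictors of the later one. When it is left out, the variance it would have explained stays in the residual, and the confidence interval for a group difference is wider than it need be, by an amount that depends on how well baseline predicts outcome.

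The arms are small (42 evaluable infants planned), so chance differences in starting motor level can be appreciable in the sample that is actually drawn. A model with baseline corrects the realised estimate for such differences; the stated model does not. At stake is how efficiently a small trial uses data that it already collects. The validity of its test is not in question.

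**Working it through.** **Inputs from the article.** The target is 0.5 SD: "A difference of the motor quotient score among the three groups of 0.5 SD is considered to be clinically significant". The evaluable number comes from "we must recruit 42 infants in each group to have an 80% chance of detecting this difference", with alpha 0.05 two-sided. Recruitment is 49 per arm to allow for attrition. The article gives no correlation between baseline and later scores, so every r below is an assumption.

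**The plan's own figure.** I could not obtain 42 per arm from these inputs by a standard calculation. A two-sided pairwise t test at 0.5 SD and 80% power needs 64 per arm. A three-group F test with one group 0.5 SD apart (f = 0.5 × √2 / 3 = 0.236) needs 59. This is a separate matter and the present point does not depend on it. It does mean that the starting power for a pairwise comparison at 42 per arm is below 80%, so unused precision matters more.

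**Effect of a baseline term on precision.** Let r be the partial correlation of baseline with outcome, given group, diagnosis, gender and SES, and let SD be the residual SD with those terms already in the model. Adding baseline multiplies the residual variance by (1 − r²). The standardized difference becomes d = 0.5 / √(1 − r²), and the equivalent sample size without a baseline term is 42 / (1 − r²). Power is from the noncentral t distribution with 82 degrees of freedom and noncentrality d × √(42/2).

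| Assumed r | Variance removed (r²) | d | Power at 42 per arm | Equivalent n per arm |
|---|---|---|---|---|
| 0 (no baseline term) | 0% | 0.500 | 62.0% | 42 |
| 0.2 | 4% | 0.510 | 63.7% | 43.8 |
| 0.3 | 9% | 0.524 | 66.0% | 46.2 |
| 0.5 | 25% | 0.577 | 74.4% | 56.0 |
| 0.6 | 36% | 0.625 | 80.8% | 65.6 |

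The three-group F test, with one group 0.5 SD apart, shows the same pattern at 42 per arm: 64% at r = 0, 66% at 0.2, 69% at 0.3 and 78% at 0.5.

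**Size of chance baseline differences.** The standard error of the baseline difference between two arms is √(2/42) = 0.218 SD, or √(2/49) = 0.202 SD at the number recruited. For one contrast, the probability of a difference beyond 0.3 SD is about 17% at 42 per arm and 14% at 49. For either exercise arm against control it is about 29% at 42 per arm. A difference of one standard error moves the estimate by r × 0.218 SD: 0.04 SD at r = 0.2, 0.07 SD at r = 0.3 and 0.11 SD at r = 0.5, against a target of 0.5 SD. This variation is already contained in the standard error of the analysis without baseline. It is the same cost as the lost precision, seen in one realised sample, and must not be added to it.

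**The case against.** The case for leaving the plan alone has five parts.

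- **The list may not be complete.** The sentence on analysis of covariance names no covariates; the list comes in the next sentence, on adjusted means. An article condenses a longer plan, and a fuller specification might include baseline. It is still the only adjustment set given, and it is given by name. A reader who assumed that baseline was implied would be adding a term that the text does not contain.
- **The gain may be small where it matters most.** The motor aim is at 24 months CA, 23 months after baseline, and the correlation over that interval in infants may be low. At r = 0.2, power rises by less than two percentage points. This stands, and it limits the size of the point.
- **The relevant r is partial.** If diagnosis already explains part of the 1-month score, a marginal correlation overstates the gain. This stands, and the table should be read with partial r.
- **Not every outcome is affected.** Exercise-related adverse events have no baseline score. The Ross score must be below 3 at entry on a 0 to 12 scale, so its baseline range is restricted. This stands too.
- **The 1-month visit is already recognisable as baseline.** The Outcome measures section speaks of "The baseline and follow-up evaluations will be performed by experienced pediatric assessors" in one sentence with the visit ages. Relabelling it under the primary outcome is largely cosmetic.

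A reader might infer something stronger: that omitting baseline biases the comparison, inflates the type I error, or widens the interval for every outcome. The article does not support that. Randomization makes the comparison unbiased on average without a baseline term, chance imbalance is already part of its standard error, and some outcomes would gain little or nothing.

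**Conclusion.** The point holds as a matter of efficiency. The stated model adjusts for diagnosis, gender and SES but not for a pre-randomization value of the outcome that the trial collects. The randomized comparison remains valid.

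For a 0.5 SD pairwise difference at 42 per arm, adding baseline would raise power from 62% to between 64% (r = 0.2) and 74% (r = 0.5). These figures rest on assumed partial correlations, on a two-arm comparison, and on reading the 0.5 SD against the residual SD of the planned model. For the 24-month motor quotient the lower end is the prudent expectation. Larger gains are likely at 4 and 6 months and for growth and bone measures, but the article has no data to confirm this. That secondary outcomes have a 1-month value is inferred from the common visit schedule in the Study design and Outcome measures sections; their own section does not repeat the visit times.

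The change is worth making because it is almost free, although its benefit for the main aim is uncertain.

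**What to change.** In the Statistical analysis section, add the 1-month CA value of the same outcome to the covariates, next to diagnosis, gender and SES. Do this for the PDMS-II motor quotient and for each continuous secondary outcome with a baseline measurement: ventricular function, bone speed of sound, weight, body length, and head and upper arm circumference. Include the Ross score where its restricted entry range leaves enough variation. Do not apply it to adverse events. State that the 1-month score is the baseline, and that the outcome times are 4, 6, 12 and 24 months CA.

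The cost is one degree of freedom per model, with about 126 evaluable infants (3 × 42), and no new visits, data or patients. Because randomization follows the baseline assessment, the covariate should be nearly complete. Recruitment is already underway, so the change should be written down before outcome data are examined by group; otherwise it could look data-driven.

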## Study design

The CHD patients with cardiac catheterization will be recruited from and investigated at the Xin Hua Hospital affiliated to the Shanghai Jiao Tong University School of Medicine, Shanghai City, China.

Prior to inclusion, the following information will be obtained for all patients: demographic data (for example, gestational age at birth, birth weight, CA, and gender), medical history (for example, the duration of intensive care unit and hospital stay, and age of cardiac catheterization), heart defect (for example, defect type and size), and type of feeding (for example, breast or artificial feeding). Each patient’s parents will be asked to sign an informed consent form before the patient can participate in the study.

Eligible participants will be randomized by a 1:1:1 allocation ratio by computer either to the exercise intervention group, in which they will receive passive movement and active exercise to promote motor development; the home-based intervention group, in which they will receive passive movement and active exercise from parents or caregivers at home; or the control group, in which they receive follow up only (Fig. 1). The total study duration will be 23 months, which consists of a 3-month intervention and 20-month follow-up period without intervention. All patients will receive the exercise intervention, the home-based intervention, or the control conditions as allocated. All patients will be assessed at 1, 4, 6, 12 and 24 months CA.

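### Intention-to-treat is made conditional on loss to follow-up and offered as the handling of lost infants, which it cannot be under the stated ANCOVA

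*Protocol article*

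**What the plan says.** The Statistical analysis section of the protocol article states the comparison as "We will use analysis of covariance to compare the primary and secondary outcomes of the three groups". It is fitted through a general linear model "with the group as the fixed factor and diagnosis, gender and SES as covariates". On patients who are lost, the section has one sentence: "If patients are lost to follow-up, an intention-to-treat analysis will be performed". Intention-to-treat is not mentioned anywhere else in the article.

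Three other sections bear on this:

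- Study design: "All patients will be assessed at 1, 4, 6, 12 and 24 months CA". The Methods/Design aims name motor development at 24 months corrected age as the target.
- Sample size calculation: "Considering potential attrition, 49 infants in each group will be recruited". The number before attrition is 42 per group, and no attrition rate is given.
- Withdrawal management: infants may leave, or be asked to leave, the study at the parents' request, for heart failure, respiratory failure or other serious disease, or because the exercises caused adverse effects.

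**The concern.** The sentence has two faults, and both lie in what it states.

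First, it attaches a condition to something that should have none. Analysis as allocated protects the randomised comparison against non-compliance and added treatment as well as against loss. The article foresees both of these. Refusal to take part is a compliance category in each exercise arm, and the Study design section lets a pediatrician prescribe additional physiotherapy. Such departures can occur in an infant who attends every visit, yet the rule is written only for the case where patients are lost.

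Second, it offers intention-to-treat as the answer to lost patients. The principle says that a lost infant still belongs to the comparison. It does not say what score that infant should have. A team following the sentence literally could run the stated model on the available scores and report the result as intention-to-treat.

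At stake is bias in the primary contrast. Follow-up runs for 20 months after the 3-month intervention. One withdrawal reason, adverse effects of the exercises, can arise only in the two exercise arms. Another, serious disease, is plausibly related to motor development.

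**Working it through.** **1. The attrition allowance.** From the Sample size calculation section, the plan needs 42 per group and recruits 49. The implied loss is 1 − 42/49 = 7/49 = 14.3%. Dividing back, 42/(1 − 1/7) = 49, so the two figures agree. Over three groups this is 3 × 7 = 21 of 147 infants, leaving 126. The rate is inferred, because the article does not state one. How the 42 was obtained is a separate question and is not used here.

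**2. What the stated model can use.** The stated terms are group, diagnosis, gender and SES. The article names no repeated-measures term and no imputation. A general linear model of the 24-month quotient on these terms needs an observed 24-month quotient for each infant. With the planned attrition and nothing added, a 24-month comparison would therefore rest on about 126 of 147 infants.

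**3. What the conditional wording covers.**

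| Situation | Does the sentence apply? | Does it settle the analysis? |
|---|---|---|
| All infants followed, some refuse exercise or get added physiotherapy | No | Analysis as allocated is implied by the group factor but not stated |
| Some infants lost | Yes | Group membership yes, missing scores no |

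**4. How large the bias could be, under assumed figures.** The documents give no rate of selective loss, so this step is an illustration only. If a fraction d of an arm is lost, the mean of those who stay differs from the mean of the whole arm by d × (mean of those who stay − mean of those lost).

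A simulation with 49 infants per arm, 2,000 repetitions and no true difference removed the same number from two arms. Removal was at random in one arm. In the other, the chance of loss was proportional to exp(−g × score in SD units). The spurious difference in favour of the selectively depleted arm, in SD, was:

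| Lost per arm | g = 0.5 | g = 1.0 |
|---|---|---|
| 7 of 49 (implied by the plan) | 0.08 | 0.14 |
| 10 of 49 (assumed) | 0.12 | 0.20 |
| 15 of 49 (assumed) | 0.16 | 0.30 |

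The formula explains the first row. With d = 1/7, the unrounded shifts of 0.077 and 0.137 SD mean that the lost infants scored 7 × 0.077 = 0.54 and 7 × 0.137 = 0.96 SD below those who stayed. The plan's own target difference is 0.5 SD. If infants who are doing well leave instead, the sign reverses.

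**The case against.** The strongest reply is that the article nowhere says infants without a score are dropped. Promising an intention-to-treat analysis when patients are lost reads as an intent to keep them. This is a condensed article, and a full protocol or analysis plan may specify imputation. That stands. A reader might infer that the intention-to-treat result is certain to be a complete-case result, and the text does not support so firm a statement. The absence of a named missing-data method is not charged here either. What is charged is the published sentence, which presents the wrong tool as the handling of loss.

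A reader might also infer that, with complete follow-up, infants would be regrouped by the treatment they actually received. Nothing says so. The groups are defined by randomisation, group is the fixed factor, and no per-protocol or as-treated set appears. Because attrition is expected, the condition will probably be met anyway. The remaining fault is that the rule is written as conditional when it should not be.

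Nor does the article say that the 4-, 6- and 12-month scores go unused. It does not tie the analysis of covariance to one visit. The narrower point holds: the model as stated does not carry an infant's earlier scores into a 24-month comparison.

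Finally, it is tempting to express the fault as power lost between 49 and 42 per group. That difference is the cost of attrition, which the sample size section already allows for. Rewording the sentence would not recover it.

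**Conclusion.** The point holds in this form: the sentence makes a rule conditional that should be unconditional, and it uses that rule for a task it cannot do. An analysis plan that put this right would have to depart from the published sentence.

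Unless such a document exists, a 24-month comparison by the stated model would omit about 21 of 147 infants (14%). This assumes that the attrition implied by 42 and 49 occurs and that it falls on the 24-month score. The withdrawal criteria give concrete reasons why the omission could depend on arm and on outcome. The resulting bias cannot be computed from the article. Under the assumptions shown it is about 0.08 to 0.14 SD at the implied attrition, and up to 0.30 SD at 30% loss. That is enough to justify changing the text, but it does not show that the result will be biased.

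**What to change.** Replace the sentence with two separate statements.

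*Analysis set:* all randomised infants are analysed in the group to which they were allocated, regardless of compliance, added physiotherapy or stopping exercise. This is a rule for analysis only and leaves the withdrawal criteria as they are.

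*Missing scores:* the primary 24-month group contrasts come from a repeated-measures mixed model on the 4-, 6-, 12- and 24-month motor quotients, with group, visit, group-by-visit, baseline quotient, diagnosis, gender and SES. Add one sensitivity analysis for data missing not at random, for example imputing missing 24-month scores and lowering them in the two exercise arms by increasing amounts until the conclusion changes.

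The model uses scores already scheduled and can be fitted in SPSS, which the article already names. No visit, infant or procedure is added, and recruitment is still underway.

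The cost is a little more analysis work and a missing-at-random assumption in the primary model, which the sensitivity analysis probes. An infant lost before the 4-month visit has no score after baseline. That infant adds nothing to the mixed model and enters only through the imputation, so the number of such infants should be reported by arm.

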## Discussion

According to previous studies, exercise is an effective treatment for adolescents and adults with CHD. However, the evidence of the effects of exercise for CHD infants with cardiac catheterization is sparse. We will perform a prospective randomized-controlled trial of passive movement and active exercise for very young CHD infants with cardiac catheterization. The chosen method seems safe, applicable and feasible to very young infants with CHD. The study may provide evidence that passive movement and active exercise offer an alternative treatment for very young infants with CHD. Passive movement and active exercise may have some beneficial effects for infants with CHD by promoting motor development and growth, and improving heart function and bone quality.

This study has some strengths. First, the follow-up duration in most previous exercise studies typically ranged from 12 weeks [23] to 1 year [20]. In this study, the total study period is 23 months, with an intervention duration of 12 weeks and a follow-up duration (with no active intervention) of 20 months. Second, in this study, the intervention group performs exercises with the assistance of experienced pediatric physiotherapists, meanwhile the home-based intervention group performs exercises with the assistance of parents or caregivers, but the control group receives no training. Therefore, compared to previous studies [18–20, 23], our study could reduce biases. Third, a power calculation is performed for this study. The total number of patients enrolled in the study is 147. Fourth, previous studies have mainly focused on exercise capacity [10, 18–20] and motor development [23]. Heart function and bone quality are rarely analyzed following passive movement and active exercises in patients with CHD. However, there are some limitations in our study. The spontaneous daily activities outside the study exercises are not monitored. Parents or caregivers may alter their infants’ daily activities, which would influence motor development.

## Trial status

Subject recruitment is underway.

## Abbreviations

CHD: Congenital heart disease
CA: Corrected age
PDMS-II: Peabody Developmental Motor Scales-II
SOS: Speed of sound
